# Practical health co-operation - the impact of a referral template on quality of care and health care co-operation: study protocol for a cluster randomized controlled trial

**DOI:** 10.1186/1745-6215-14-7

**Published:** 2013-01-07

**Keywords:** Cluster randomized trial, General practice, Quality of care, Referral

## Abstract

**Background:**

The referral letter plays a key role both in the communication between primary and secondary care, and in the quality of the health care process. Many studies have attempted to evaluate and improve the quality of these referral letters, but few have assessed the impact of their quality on the health care delivered to each patient.

**Methods:**

A cluster randomized trial, with the general practitioner office as the unit of randomization, has been designed to evaluate the effect of a referral intervention on the quality of health care delivered. Referral templates have been developed covering four diagnostic groups: dyspepsia, suspected colonic malignancy, chest pain, and chronic obstructive pulmonary disease. Of the 14 general practitioner offices primarily served by University Hospital of North Norway Harstad, seven were randomized to the intervention group. The primary outcome is a collated quality indicator score developed for each diagnostic group. Secondary outcomes include: quality of the referral, health process outcome such as waiting times, and adequacy of prioritization. In addition, information on patient satisfaction will be collected using self-report questionnaires. Outcome data will be collected on the individual level and analyzed by random effects linear regression.

**Discussion:**

Poor communication between primary and secondary care can lead to inappropriate investigations and erroneous prioritization. This study’s primary hypothesis is that the use of a referral template in this communication will lead to a measurable increase in the quality of health care delivered.

**Trial registration:**

This trial has been registered at ClinicalTrials.gov. The trial registration number is NCT01470963

## Background

Quality of healthcare is defined by the American Institute of Medicine as ‘the degree to which health services for individuals and populations increase the likelihood of desired health outcomes and are consistent with current professional knowledge’ [1]. The focus on prevention of medical errors and improved quality of medical care continues to increase [2,3]. This focus is evident in Norway by the publication of a national strategy for quality improvement in health and social services [4], and the multitude of clinical guidelines available from governmental and professional sources.

The referral of a patient from a general practitioner (GP) to a hospital environment represents a transition of care, in which the major information exchange is through the written referral letter [5]. This transition of care represents an important step in the quality of the care process, and it has been shown that key clinical information may not be communicated adequately at the transition of care interface [6]. There has been considerable research into the quality of a referral and its impact on the process of care. A Norwegian study from 2007 amongst elderly patients demonstrated that both referral and discharge letters were missing vital information [7]. The consequences might represent a health hazard to older patients [7]. A Finnish assessment of the quality of referral letters for patients with asthma concludes that 45% of the referrals were of poor or unacceptable quality, based upon quality criteria developed by GPs and hospital respiratory consultants [8]. Others have also found varying quality and content of referrals [9-15].

Many studies have been designed for improving the referral process from GPs to the hospital [16,17]. A recent Cochrane review on interventions to improve outpatient referrals from primary to secondary care concludes that surprisingly few interventions on the referral system have been rigorously evaluated. Many of the studies evaluated focused only on referral rates or referral quality. The review highlights the complexities of research in this area, especially as no single study managed to present findings on all aspects of the referral process (referral behavior, management of non-referred patients, secondary care management of patients, the flow of patients through the referral system, patient outcomes and satisfaction, and resource use). However, structured referral sheets and local education interventions have an impact on referral rates [18].

The primary objective of the present study is to evaluate whether the implementation of a referral template in the referral from general practice to hospital care can lead to a measurable increase in the quality of care delivered at the hospital. As secondary objectives, we will assess patient satisfaction and effective prioritization at secondary care.

## Methods

### Study design

This study is a cluster randomized trial, with the GP clinics as the cluster. The local GP clinics are randomly assigned either to use a referral template or to continue standard referral practice.

### Participants

The 14 community GP practices in the area primarily served by University Hospital of North Norway Harstad (UNN Harstad) were included in the randomization process, with a total list size of 35,490 patients. In Norway, each individual has a regular GP. These GPs act as gatekeepers to secondary care. The health care system is relatively uniform throughout the country. In the study area, access to specialist care is practically impossible without a GP referral, whereas some access is possible in other areas of the country.

The study population will consist of patients referred to the medical department at UNN Harstad. The referrals received are, almost exclusively, electronic. Children (<18 years of age) and patients with reduced capacity to consent will be excluded from participation in the study.

### Randomization

The GP clinics were randomized stratified by location, to ensure adequate selection of cases and equal sociodemographic background data. Five of the centers are larger town-based centers and nine are smaller, more rural centers. The location of the center was not expected to influence the outcome variables. Initially, two centers approached declined the invitation to participate in the study, and therefore two additional GP clinics were randomly selected, as illustrated by Figure 1.

**Figure 1 F1:**
[figure not shown]
**Flow chart of randomization process.** ‡ From the four rural clinics initially randomized to the intervention group, two clinics refused. Therefore two additional rural clinics, from the five rural clinics initially randomized to the control group were randomized, and consented to, the intervention.

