### Statistical methods

We will collect the following baseline characteristics:

• patient age (mean and confidence interval) and sex (number and percentage)

• practice list size (median and interquartile range, or mean and confidence interval if normally distributed)

• referral type - electronic or paper (number and percentage)

• referred by - GP or other doctor (number and percentage).

For the primary outcome (quality score), we will calculate adherence scores as described above and compare between treatment arms. We expect substantial variation in cluster size. Because of the small number of clusters, analysis based upon the cluster level was considered [41]. However, as there is no prior accurate estimate of variation between clusters, weighting for cluster size could not be achieved [41]. To offer increased precision and take into account between-cluster variation, random effects linear regression will be used [42] to generate estimates of intervention effect. It has been suggested that this can be used for studies with as few as 10 clusters [36]. The estimated effect and confidence intervals will be reported. A *P*-value <0.05 will be regarded as statistically significant. Intention to treat analysis will be employed.

The referrals will be scored using a simple scoring system related to the referral templates. Each unit of information specified in the referral template (for example, presence of weight loss specified) will provide one point in the scoring system, with no weighting applied. Scores will be compared between the groups as noted above.

For outcome severity, random effects linear regression will be used, with the severity group score as a categorical variable, and the relationship compared between the intervention and control group.

In the questionnaire, answers noted as ‘not applicable’ or no answer will be counted as missing data. The questionnaire will be scored according to a pre-set scoring system. Scores will be analyzed using the regression technique outlined above. The data will also be analyzed to determine if factors such as self-perceived health, age, gender, and education level have an impact on patient experience.

The trial will be reported according to the CONSORT standards for reporting cluster randomized trials [43].

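### Two clinics refused after allocation and two control clinics were switched in their place, so a comparison of the final arms is not intention to treat, and the plan does not say which allocation it means

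*Protocol article*

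**What the plan says.** The Participants section says of the 14 practices: "The 14 community GP practices in the area primarily served by University Hospital of North Norway Harstad (UNN Harstad) were included in the randomization process". The Randomization section gives the strata: "Five of the centers are larger town-based centers and nine are smaller, more rural centers". The abstract reports that "seven were randomized to the intervention group".

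The sequence of events is in the Figure 1 legend: "From the four rural clinics initially randomized to the intervention group, two clinics refused", after which "two additional rural clinics, from the five rural clinics initially randomized to the control group were randomized, and consented to, the intervention". The Randomization section describes the same event more briefly. It says that "two centers approached declined the invitation to participate in the study" and that two further clinics were selected at random. It does not say that these came from the control arm.

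The Statistical methods section states: "Intention to treat analysis will be employed". It does not say whether the first or the final allocation defines the arms.

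**The concern.** By the legend's own account, allocation came first, refusal second and reassignment across arms third. The two refusers left the intervention by their own decision, and two clinics first allocated to control now use the template. Every clinic in the final intervention arm has therefore agreed to take part. Nothing in the text says that clinics remaining in control were asked, or selected, in the same way.

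Willingness to adopt a referral tool may be related to how a clinic refers, and so to the scored care process. If it is, the final-arm contrast mixes the template's effect with that difference. More patients do not remove it, and the planned random effects regression, as described, has no term for it. The Discussion considers bias arising after randomisation only for patient recruitment, not for refusal by clinics. An unqualified intention-to-treat label would tell readers that the randomised comparison had been preserved when, by final arms, it had not.

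**Working it through.** **Inputs from the document.** 14 clinics: 5 town and 9 rural. Seven in the intervention arm. Rural stratum at the first draw: 4 intervention, 5 control. Two of the 4 refused, and two of the 5 were switched. Target difference in the quality score: 10%.

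**Step 1: reproduce the counts.** Rural 4 + 5 = 9, and 9 + 5 town = 14, as stated. The replacement was two for two, so the rural intervention count stays at 4. That leaves 7 - 4 = 3 town clinics in intervention and 5 - 3 = 2 in control (derived, not stated).

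| | Intervention | Others |
|---|---|---|
| First allocation | 4 rural + 3 town = 7 | 5 rural + 2 town = 7 |
| Final, refusers counted as controls | 2 + 2 switched rural + 3 town = 7 | 3 rural + 2 refusers + 2 town = 7 |
| Final, refusers dropped | 7 | 3 rural + 2 town = 5 |

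The text shown does not say which of the last two rows applies. In either case 2 + 2 = 4 of the 14 clinics do not have the arm or condition they first drew.

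**Step 2: contrast kept under first allocation.** Assume full uptake in consenting clinics, none elsewhere, and refusers' patients followed up. Formula: exposed share of first intervention arm minus exposed share of first control arm.

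- Equal cluster sizes: 5/7 - 2/7 = 3/7 = 43%. A true 10-point effect would appear as about 4.3 points.
- Patient weighting, town clinics assumed twice as large: (2 + 3×2)/(4 + 3×2) - 2/(5 + 2×2) = 8/10 - 2/9 = 58%.

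**Step 3: possible shift under final allocation (illustration only).** Let D be the gap in mean quality score between willing and refusing clinics. The document gives no value. Treat the two known refusers as the only unwilling clinics, and count them as controls. Formula: shift = (refusers' share of the control arm) × D.

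| Assumed D | Equal weights, 2D/7 | Town clinics twice as large, 2D/9 |
|---|---|---|
| 5 | 1.4 | 1.1 |
| 10 | 2.9 | 2.2 |

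The sign of the shift is the sign of D, which is unknown.

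**The case against.** Several points on the other side have weight.

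- **The event is disclosed and the replacements were drawn at random.** True, and it rules out hand-picking. It does not undo the self-selection of the two refusers or the requirement that replacements consent.
- **Intention to treat might mean first allocation.** A reader might infer that the document flatly contradicts itself. It does not: the term is undefined, and first allocation remains open. The fault is that the sentence does not fit the final arms and does not say which arms it means.
- **The refusers may not be in the control arm.** A reader might infer from 14 clinics and seven in the intervention that they must be. But 14 is the number entering randomisation, not the number analysed, so 7 v 5 is equally compatible. The flow chart is not shown and may settle this. If the refusers were dropped, consenting clinics are still compared with clinics of untested willingness, and two randomised clusters are lost.
- **The bias need not favour the template.** A reader might infer that refusers are the poorer clinics. Clinics content with their own referrals could also decline. The document supports neither direction.
- **The illustrated sizes may be generous.** The outcome is hospital care, scored blind, in one hospital. With the document's ICC range of 0.001 to 0.08 and an assumed score SD of 20, the between-clinic SD is √0.001 × 20 = 0.6 to √0.08 × 20 = 5.7 points. D = 10 is then about 1.8 or more clinic SDs. The affected clinics are also rural, which the document calls smaller, so they may carry less weight.
- **Sensitivity analyses are often left to the analysis plan.** Fair. But the reallocation and the intention-to-treat statement both stand in this article, and it is their fit that is at issue.

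**Conclusion.** The point holds as a fault of definition and labelling that affects what the primary comparison means. Refusal after allocation and replacement from the control arm are stated outright, so an analysis by final arms cannot be called intention to treat, and the plan does not say that it will use any other.

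The number of clinics affected, 4 of 14, follows directly from the document. The rest is conditional. First allocation keeps about 43% of the contrast with equal cluster sizes and full uptake, and about 58% under patient weighting with town clinics assumed twice as large. A shift of 1.4 to 2.9 points rests on an assumed D of 5 to 10, equal clinic weights and the refusers being counted as controls. No direction or actual size of bias is established. What is established is that the choice of allocation can materially change the estimate, and that it is left open.

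**What to change.** In the Statistical methods section, replace the single intention-to-treat sentence with the following:

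1. Define intention to treat as all clinics by first allocation, as far as patients of the refusing clinics are enrolled, and report this estimate beside the main result.
2. Call the final-arm comparison an analysis as re-allocated, not intention to treat.
3. If the refusers are counted as controls, add a sensitivity analysis of the final arms without them. Note that it does not remove the one-sided consent.
4. State in which arm, if any, the two refusers are counted, and say in the Randomization section that the replacements came from the control arm.

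The cost is rewording and up to two extra model runs. No change to conduct is needed, which matters because inclusion began in 2011. If patients of the refusing clinics were not enrolled, the first-allocation analysis cannot be complete and the report should say so. The downside is that the first-allocation estimate is diluted and less precise, so it should accompany the main result and be read with the dilution stated.

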### Recruitment

New patients referred to the medical department within one of the four diagnostic groups described below will receive written information and a consent form together with their appointment letter. These will be sent out by a clinic nurse unaware of the status of the GP center sending the referral (intervention or control). Patients will be orally reminded at the appointment and may be given a new consent form. This process is illustrated in Figure 2.

**Figure 2 F2:**
[figure not shown]
**Recruitment process.** Recruitment of patients in both the intervention and control groups follow the same procedure.

### Intervention

The referral templates have been developed based upon international literature [19-27] and in collaboration with local specialists in the appropriate medical field. The templates have also been through a process of clinical assessment from subspecialists in other northern Norwegian hospitals. In acknowledging the problems in earlier studies with the uptake of referral interventions [17,18] we have deliberately reduced the number of items in the referral templates, to ensure ease of uptake. Only information that the medical consultants thought imperative in the referral have been included as items in the templates. The study will implement referral guidelines for the following four diagnostic groups:

•
patients referred with dyspepsia;

•
patients referred with suspected colonic malignancy;

patients referred with chest pain;

•
patients referred with chronic obstructive pulmonary disease or suspected chronic obstructive pulmonary disease.

These diagnostic groups were chosen as they represent a substantial number of the referrals to a medical department (own data, 2008). They also represent a clear diagnostic challenge in primary care and are adept for simple referral guidelines.

The GPs at the intervention offices will use the referral template when initiating a new referral process for a patient. To ensure adequate uptake of intervention, the templates have been distributed as electronic templates as well as hard copies. The templates function as guidelines, but are not implemented as compulsory electronic checklists. The intervention referrals are sent to a separate electronic inbox at the hospital. The further evaluation and process of care has not been altered in the intervention group compared with the standard referral practice in the control group (Figure 3).

**Figure 3 F3:**
[figure not shown]
**Referral pathway.** Flow of referral and process of care in the intervention (blue arrows) and control group (red arrows).

In addition, questionnaires have been developed that assess patient experiences within the care framework, with one questionnaire designed for inpatients and one for outpatients. These questionnaires have been produced by combining questions from previously validated questionnaires regarding patient experiences in general and with transitional care. They include questions from a Norwegian patient experiences questionnaire [28]); two questions about health interaction from the Commonwealth Fund Survey 2010 [29]; the Care Transitions Measure 3 [30]; and demographic questions.

The questionnaires have been reviewed through an interview process with patients. This was done to ensure that the forms are acceptable to patients and to highlight possible issues that patients felt were missing from the questionnaires.

### Objectives

We aim to examine the impact of a referral template on the process of care, at the individual level. The primary hypothesis is that the use of a referral template in the communication between the GP and secondary care will lead to a measurable increase in the quality of health care delivered. Secondary hypotheses include that the use of a referral template in the communication between a GP and secondary care will lead to:

a • measurable improvement in referral quality;

• a change (up or down) in the number of patients defined as being in need of prioritization (as defined in national guidelines for prioritization in health care [20,23,24]);

• more appropriate prioritization, as measured by final diagnosis;

• an increase in the ‘appropriateness’ of the referrals (positive predictive value (PPV) of referral [31];

• and better patient satisfaction, as measured by self-report questionnaires.

### Outcomes

The primary outcome will be a quality indicator score compared between the intervention and the control group. The quality indicators have been generated from previous international quality assessment tools and national and international treatment guidelines. Some adaptation to locally accepted practice has been made, as demonstrated by others when quality indicators are used in a new context [32]. Each patient care process will be scored according to the criteria. Scoring will be done by a panel of specialists blinded to the intervention status of the patient. We will calculate the quality score as adherence scores (number of quality criteria met divided by number of applicable criteria expressed as a percentage) as illustrated by Ashton *et al*. [33]. If a criterion is applicable, but no information can be found (applicable, but not answerable), it will be noted ‘not met’ for statistical purposes [34]. Weighting of the criteria based upon clinical importance will not be used, as this adds complexity without adding much to the clinical findings, a finding discussed by Lyons and Payne in 1975 [35]. The scores will be compared between the intervention and control groups.

As secondary outcomes, the quality of the referrals will be evaluated against the developed referral template, to determine if the intervention has led to improved referral quality. It is important to measure referral quality, as the premise in the study is that more information will lead to improved care. In addition, health process outcomes such as waiting time from referral to appointment, number of appointments before a diagnosis is reached, time before treatment is initiated, the application or not of appointment prioritization, and the outcome of any given referral (appointment, return information or referral rejected) will be collected and compared between the groups. Bennett *et al*. used the PPV of a referral as a measure of the appropriateness of the referral [31]. In adapting this concept from glue ear in otolaryngology to a medical department we have defined it as the proportion of the GP referrals that result in a histological diagnosis, diagnostic clarification or change in medical management. We will assess and compare the PPV of referrals in the study groups. Patient experiences will be compared between the intervention and control group. Finally, the possible outcome diagnoses have been grouped according to severity. We will correlate the continuous outcome variable ‘waiting time’ with the grouped severity, to see whether the prioritization in the intervention group is more aligned with disease severity.

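### Appropriateness of prioritisation is tested only through realised waiting time against final severity; the recorded prioritisation decision is collected but never related to severity

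*Protocol article*

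**What the plan says.** The Objectives section of the protocol article lists, among the secondary hypotheses, "more appropriate prioritization, as measured by final diagnosis". A separate hypothesis concerns a change, in either direction, "in the number of patients defined as being in need of prioritization".

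The Outcomes section includes "waiting time from referral to appointment" and "the application or not of appointment prioritization" among the process outcomes to be compared between groups. For appropriateness it says that "the possible outcome diagnoses have been grouped according to severity". The test it then sets out is this: "We will correlate the continuous outcome variable ‘waiting time’ with the grouped severity". The declared purpose of that correlation is "to see whether the prioritization in the intervention group is more aligned with disease severity".

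Statistical methods repeats this as a random effects linear regression with severity group entered as categories, and compares the relationship between arms. Data gathering takes waiting times from automated reports once the care process has ended. The recorded prioritisation decision is not related to severity or final diagnosis anywhere in the article.

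**The concern.** The variable analysed is not quite the thing inferred. The template changes what the hospital knows when it assesses the referral, so its direct effect is on the priority given at that point. The realised wait starts from that decision but also reflects later changes to the booking.

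Consider a patient with a severe final diagnosis who was given low priority but was then seen early for some other reason. The planned measure pairs a short wait with high severity and counts the case as good prioritisation. The arm with more under-triage has more patients who can be reclassified in this way, so a real improvement in triage would be understated. The decision itself is collected, but it is used only to compare how often it is made in each arm, which cannot show whether it was made for the right patients.

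**Working it through.** The plan states no figure for this outcome, so there is nothing to reproduce. The check has two parts.

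**1. The text, side by side**

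| Element | What the article fixes |
|---|---|
| Hypothesis (Objectives) | Appropriateness of prioritisation, judged by final diagnosis |
| Variable standing for prioritisation (Outcomes, Statistical methods) | Realised waiting time, continuous |
| Yardstick (Outcomes) | Severity group of the final diagnosis |
| Prioritisation decision (Outcomes) | Collected as applied or not; compared between arms; not crossed with severity |
| Means of separating early triage from later rebooking | None stated |

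**2. How far the contrast could shrink**

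All inputs here are assumptions; none is in the article. Among patients with a severe final diagnosis, let *W_P* be the mean wait if prioritised, *W_N* the mean wait if not, *W_R* the mean wait of a non-prioritised patient who is brought forward, and *r* the fraction of non-prioritised severe patients brought forward (the same in both arms). Let *d* be the between-arm difference in the proportion of severe patients prioritised.

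- Contrast without early appointments: *d*(*W_N* − *W_P*)
- Contrast with them: *d*[(1 − *r*)*W_N* + *r* *W_R* − *W_P*]
- Share lost: *r*(*W_N* − *W_R*)/(*W_N* − *W_P*)

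First set of inputs: 70% prioritised in control and 85% in intervention (*d* = 0.15), *W_P* = 20, *W_N* = 100, *W_R* = 30 days.

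- No early appointments: 0.15 × 80 = 12.0 days.
- With *r* = 0.30: the non-prioritised mean is 0.7 × 100 + 0.3 × 30 = 79. Control is 0.7 × 20 + 0.3 × 79 = 37.7; intervention is 0.85 × 20 + 0.15 × 79 = 28.85. The difference is 8.85 days.
- Share lost in general: *r* × 70/80 = 0.875*r*.

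| *r* | Contrast (days) | Share lost |
|---|---|---|
| 0 | 12.0 | 0% |
| 0.05 | 11.5 | 4.4% |
| 0.10 | 10.95 | 8.75% |
| 0.30 | 8.85 | 26% |

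Second set of inputs, by simulation: 20% of patients severe; severe patients prioritised 60% in control and 80% in intervention; non-severe patients prioritised 30% in both; mean wait 20 days if prioritised or brought forward, 80 days otherwise. The between-arm difference in the severe-minus-non-severe wait was −12.1, −10.9, −9.0, −6.2 and −3.1 days for *r* = 0, 0.10, 0.25, 0.50 and 0.75. The formula gives −12(1 − *r*), that is −12, −10.8, −9, −6 and −3, which agrees up to simulation error. The same contrast computed on the prioritisation decision stayed at about 0.20 throughout.

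**The case against.** The strongest reply is that realised waiting time is a declared target in its own right. The Discussion says the study means to assess whether waiting times are appropriate, and the wait a patient actually had is what matters to that patient. The triage decision also has its own hypothesis and its own comparison. This stands: it justifies keeping the waiting-time analysis, and it means the prioritisation hypothesis is addressed indirectly. A reader might infer that it goes unanswered, but the text does not support that.

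Nor does the article mention appointments being brought forward, or admissions while waiting. A reader might take the questionnaires, "with one questionnaire designed for inpatients and one for outpatients", as a sign of such admissions, but inpatients may be admitted electively. It is also unclear whether an emergency contact would count as the appointment that ends the wait. The mechanism is therefore conditional.

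Two further inferences are tempting and fail. One is that severity is partly caused by the wait: the grouping is by diagnosis, nothing says that stage or clinical state is used, and progression over a long wait would score as poor alignment, opposite to the mechanism above. The other is that queues, holidays and rescheduling bias the comparison: both arms use one hospital and a shared caseload (Blinding), so this variation costs precision and is not shown to distort the contrast.

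What remains is that a more direct test is available from data already collected and is not planned.

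**Conclusion.** The point holds in a limited form. The hypothesis about appropriate prioritisation is tested only through realised wait, which mixes the decision the template can influence with later scheduling. Where under-triaged severe patients are seen early for other reasons, the bias is toward no difference.

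The size is unknown. On the first set of assumed waits it is small if early appointments are rare (4% to 9% of the effect at 5% to 10%) and material if they are common (26% at 30%). In the ranges shown the sign of the effect is kept. These figures assume the same fraction brought forward in both arms. One secondary outcome is affected; the primary analysis is not.

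**What to change.** For this hypothesis, make the recorded prioritisation decision (yes/no) the outcome and relate it to severity group by arm. Report the proportion prioritised among severe and among non-severe final diagnoses in each arm, and test the arm-by-severity term in a mixed logistic model with clinic as random effect. State that the variable is the decision made when the referral was assessed; the article implies this but does not say so.

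Keep the planned regression of waiting time on severity group, presented as a separate analysis of whether waiting times are appropriate.

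The decision and the severity group are both already planned for collection, so the change is to the analysis wording. The downsides are that a yes/no outcome is coarser than days, and that precision will be limited with 14 clinics and an unknown number of severe cases. Re-analysing waits by the originally booked date is not proposed, because the article does not list that date as collected.
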